### Objectives

The purpose of this study is to determine whether providing incentives to both support person and expectant mother, if she is able to quit smoking, is more effective than providing incentives to expectant mother only, in promoting short- and long-term smoking cessation during pregnancy. In essence, the present study seeks to answer the question: “Can partners (eg, spouse) be incentivized to be more supportive and effective quit buddies to their pregnant smoking partners?”

Specifically, the study aims to determine whether (1) providing an incentive to both the support partner and expectant smoking mother to quit is more effective than providing an incentive to the pregnant smoker alone at promoting abstinence; (2) regardless of incentives, women who receive more positive cessation support from their partners, as measured by the Partner Interactive Questionnaire 20 (PIQ-20), are more likely to quit smoking; and (3) providing incentives for pregnant smokers to quit is more effective than “usual care” antenatal quit smoking services such as brief advice and referral to smoking cessation services (external telephone counseling and smoking cessation nurse) at promoting smoking cessation.

The primary outcome for the study is smoking status (ie, smoking or quit), as determined by self-report 7-day point prevalence, and carbon monoxide (CO) less than 7 particles per million (ppm) at the end-of-pregnancy time point. Secondary outcomes include effect of incentives on long-term (2 months and 12 months postpartum) abstinence and influence of the quality of partner support (positive compared to negative supportive behaviors) on smoking status.

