### Interventions

During their initial enrolment visit (visit 1), all participants and their support partners are offered a separate resource pack providing further information and quit references. The content of the packs, selected on the basis of existing resources developed and distributed by not-for-profit organizations and government-funded bodies (eg, Quitline, Cancer Council, and SIDS and Kids), includes informational brochures on the topics of smoking and pregnancy, quitting smoking during pregnancy, a guide for quitting smoking, and smoking and sudden infant death syndrome. A referral and resources summary list (eg, further websites and available mobile phone apps) is also provided that includes telephone numbers of local counseling services. The resource pack specifically designed for partners contains information about the effect of second-hand smoke on children, quit smoking products, and how to be an effective quit buddy. Following the single-blinded, consecutive-month schedule, women are allocated to either the control or treatment group during their enrolment session (Textbox 1).

Control and Treatment group incentives.GroupControlOnly the participant is rewarded with a AUD $50 voucher if they verify as quit during monthly visitsTreatmentBoth participant (1 x AUD $50) and their designated support person (1 x AUD $50) receive a shopping voucher if the participant verifies as quit during monthly visitsIf partner is not present during study visits, participant collects both vouchers

All participants are encouraged to make a quit attempt in the 2 weeks following the enrolment visit in order to promote quit status (verified by less than 7 ppm CO breath sample) and enable incentive issue at the first monthly follow-up, although it is emphasized that each participant is able to decide their own quit timeframe and approach. No other formal smoking cessation counseling support is provided.

All participants are asked to attend 2 further study visits—visit 2 (end-of-pregnancy) and visit 3 (end-of-study)—and have the opportunity to attend monthly visits to verify their non-smoking status and receive incentive voucher/s.

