#### Enrolment Visit

During the enrolment visit (visit 1) participants are asked to complete a battery of questionnaires and provide 2 CO breath samples. Regardless of group allocation, participants are asked to nominate a support person (they are asked to have this person in mind when completing the Partner Interaction Questionnaire), preferably the person they are living with (eg, partner or family member), whose contact details are recorded along with the participant’s own details to assist with future correspondence. While no smoking cessation counseling is provided, participants are offered a resource pack for themselves and their support partner.

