#### Monthly Telephone Calls and Verification Visits

Monthly telephone calls are conducted with all participants to determine smoking status. During the phone calls, participants are asked “Have you had a cigarette (even a puff) in the past 7 days?” If a participant self-reports as abstinent, they are invited to attend a follow-up verification visit to verify their smoking status (and receive a voucher incentive), which is booked at their next convenience. If the participant self-reports smoking in the last 7 days during the monthly telephone call, they are advised that they are not eligible for the incentive that month and will be contacted again the following month. This monthly payment schedule limits the additional participation burden on participants, and where possible, is scheduled on days when they are attending routine hospital antenatal appointments. This monthly payment schedule was also utilized by the only other study published using incentivized partner support [23]. Participants who verify as abstinent at their end-of-study visit (visit 3) are eligible to receive monthly calls and incentives until 6 months postpartum. Participants who are still smoking at the end-of-study visit no longer receive monthly calls (and are ineligible for any further incentives) from that date. Multiple (up to 5) attempts are made to contact each participant for their scheduled monthly telephone calls and visits. Text messages (short message service, SMS) are also utilized to try to contact those difficult to reach. However, the study adopts an intention-to-treat approach such that if participants become un-contactable at any time throughout the study, it is presumed they are smoking [28].

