#### Smoking Knowledge Quiz

The Smoking Knowledge Quiz was developed from existing publicly available and scientifically reliable smoking information and is similar to the questionnaire used in a previous study [30]. The quiz requires participants to answer questions regarding their knowledge of the safety and effectiveness of smoking cessation treatments and techniques during pregnancy, as well as the health risks associated with cigarette smoking for themselves and their baby. Participants’ responses to this quiz are reviewed with the participant at the time of the enrolment visit to prompt discussion of health risks and available cessation aids. The quiz is administered once only at study enrolment (visit 1).

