Participants, regardless of group allocation, will be regrouped to either PIQ-POS or PIQ-NEG, as determined by the ratio of positive compared to negative support they report receiving from their support partners. The abstinence rates of these regrouped PIQ-POS and PIQ-NEG participants will then be compared at 3 time points; end-of-pregnancy, end-of-study (2 months postpartum), and 12 months postpartum.

#### Hypothesis 4

The fourth hypothesis (H4) is providing incentives for pregnant smokers to quit is more effective than “usual care” antenatal smoking cessation support at promoting smoking cessation.

The quit rates of participating women will be compared to the average quit rate of a historical control of women receiving antenatal care by the Tasmanian Health Service from 2011 to 2015 [34].

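### Aim 3 and H4 credit incentives, but the comparison with historical usual care can support a conclusion only about the whole incentive programme

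*Protocol article*

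**What the plan says.** The third aim (Protocol article, Objectives) and Hypothesis 4 (Planned Analyses) make the same claim: that "providing incentives for pregnant smokers to quit is more effective than" usual antenatal cessation care. The H4 analysis is stated in one sentence: "The quit rates of participating women will be compared to the average quit rate of a historical control of women receiving antenatal care" through the state health service from 2011 to 2015. Objectives describes usual care by example, as "brief advice and referral to smoking cessation services (external telephone counseling and smoking cessation nurse".

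Both groups are given more than vouchers:

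- Interventions: "all participants and their support partners are offered a separate resource pack providing further information and quit references". The partner's pack includes quit-buddy material. All women are also urged to try quitting within two weeks of enrolling.
- Smoking Knowledge Quiz: each woman's answers are "reviewed with the participant at the time of the enrolment visit to prompt discussion of health risks and available cessation aids".
- Verification of Smoking Status: every participant gives two expired-air CO samples.
- Monthly Telephone Calls and Verification Visits: "Monthly telephone calls are conducted with all participants to determine smoking status".

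On counselling, Interventions says "No other formal smoking cessation counseling support is provided", while Enrolment Visit says "While no smoking cessation counseling is provided, participants are offered a resource pack for themselves and their support partner".

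**The concern.** H4 names incentives as the cause of any difference from usual care. The women compared with the historical group receive vouchers together with information, a prompted discussion, encouragement and regular contact. If the H4 result is favourable and is reported in the words of the hypothesis, readers will take it as evidence on vouchers. The protocol plans to tell health professionals and the public about the results, so the wording matters to services deciding what to adopt. A service that introduced vouchers with only the checks needed to issue them would not be delivering what H4 tested.

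This is separate from how comparable the historical women are, or how their smoking was measured. Even a perfectly matched usual-care group would leave the components inseparable.

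**Working it through.** The plan gives no figure for H4, so there is nothing to reproduce. The check is one of identification.

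**1. The H4 contrast.** Let D be the participants' quit rate minus the usual-care rate. Let V be the effect of the vouchers, and C the effect of the other components over and above whatever usual care already contains. Assume additivity and, generously, no other difference between the two sets of women. Then

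D = V + C, so V = D − C.

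C is not observed in any group, because nobody receives these components without the offer of quit-contingent vouchers. One contrast cannot give two unknowns.

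**2. Whether the two study groups help.** The control group has C plus the woman's voucher. The treatment group has C plus the woman's voucher plus the supporter's voucher. Subtracting leaves the effect of the supporter's voucher, and C cancels. That is why H1 and H2 are sound on this point. It is also why they supply no information about C for H4.

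**3. What each component is.**

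| Component | Section | Needed to issue a quit-contingent voucher? | In the description of usual care? |
|---|---|---|---|
| Discussion of quiz answers | Smoking Knowledge Quiz | No | May overlap with brief advice |
| Pack for the woman (offered) | Interventions | No | May overlap with advice and referral |
| Pack for the supporter (offered) | Interventions | No | Not mentioned |
| Encouragement to quit within two weeks | Interventions | No; it is meant to make a first voucher possible | May overlap with brief advice |
| CO samples | Verification of Smoking Status | Largely yes | Not mentioned |
| Monthly calls | Monthly Telephone Calls and Verification Visits | Largely yes; they identify who is invited to verify | Not mentioned |

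After the visit at about 2 months postpartum, monthly calls continue only for women verified as abstinent. Usual care is described by example, so a component not mentioned there was not necessarily absent.

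**4. The planned checks.** Sample Size and Checks covers site effects and cyclical recruitment effects. Neither bears on C.

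**5. The protocol's own standard.** Under Partner Support and Sustained Cessation, the earlier trial of incentivized social support is faulted because its design was not fully factorial, so the contribution of partner support beyond incentives could not be isolated. H4 has the same form: a package against usual care.

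**6. Size.** The documents give neither the historical quit rate nor C. A calculation therefore shows only what assumed values imply. Assume 108 women (the H1 sample size), a fixed historical rate p0 and an exact one-sided binomial test at no more than 0.025. The smallest rejecting counts are 11, 17, 25 and 31 quitters for p0 = 5%, 9%, 15% and 20%. Suppose V = 0 and C = 5 points. The chance of a positive H4, P(X ≥ count) with X ~ Bin(108, p0 + 0.05), is then 0.52, 0.34, 0.24 and 0.22. With C = 0 it is 0.016 to 0.020. These values are conditional on the assumptions and do not estimate the voucher share.

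**The case against.** The best defence is that incentives in H4 is shorthand. The introduction speaks of incentives-based interventions and programmes, and a quit-contingent voucher cannot be issued without some check of quit status. CO testing and monthly status calls are largely part of delivering the voucher. The quiz discussion and the packs, which draw on existing public material and a referral list, may resemble what usual-care women received. H4 is also not the hypothesis the study is powered on.

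Much of this stands, and it narrows the point. It does not remove it. The protocol never defines H4 as a programme comparison. The supporter's pack, the discussed quiz and the encouragement to quit are not needed to issue a voucher, and no group separates them from it.

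Three stronger readings are tempting, but the documents do not support them.

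- *The protocol contradicts itself on counselling.* Interventions denies only other formal counselling, which is compatible with an informal discussion of quiz answers. Only the flat sentence under Enrolment Visit sits badly with the quiz section, and that is loose wording.
- *The extra components could explain the whole difference.* Nothing in the documents shows this. In the earlier randomized trial of counselling and partner support described in the introduction, six counselling calls, with or without a partner booklet and video, produced no significant difference from usual care. That does not prove a zero effect, but it gives no support to a large one.
- *Women receive CO feedback, and staff lead the quiz discussion.* The text says that readings are recorded and describes no feedback component. It does not say who reviews the quiz, although study staff is the natural reading. The packs are offered, so uptake is unknown.

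**Conclusion.** The point holds in a limited form. As worded, aim 3 and H4 attribute to incentives a contrast that can be attributed only to the whole programme, meaning vouchers and everything delivered with them. This follows from the design: all participants in both groups are allotted the same non-voucher components, so no later analysis of these data can separate them. It needs no assumption about how large those components' effects are. It rests on reading the quiz discussion, the packs and the encouragement as at least partly additional to usual care. The protocol neither confirms nor rules that out.

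The size of the voucher share cannot be estimated from the documents. The consequence is confined to what H4 may conclude. The counselling wording is a minor matter of consistency.

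**What to change.** Reword aim 3 and H4 along these lines: *an incentive programme (quit-contingent vouchers with resource packs for the woman and her supporter, a reviewed knowledge quiz, encouragement to attempt quitting, CO monitoring and monthly calls) compared with historical usual care*. State that the H4 conclusion applies to that programme as a whole.

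As a minor correction, bring the Enrolment Visit sentence on counselling into line with the Interventions wording, and mention there the discussion described under Smoking Knowledge Quiz.

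No new data, procedure or analysis is needed. Recruitment has closed, but results are still to be published, so the claim can be scoped in time. The cost is that the trial gives up the claim that vouchers by themselves outperform usual care.

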## Methods

### Trial Design

This study will adopt a non-randomized, single-blinded, controlled 2-group (control and treatment) trial design.

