### Participant Recruitment

All eligible pregnant women who smoke and live in Tasmania (Australia) are invited to participate in the study. Statewide recruitment is facilitated by drawing on data from the Tasmanian Health Service’s digital medical record (DMR) and encompasses multiple strategies to maximize reach. A research midwife, with access to the Tasmanian Health Service’s DMR, conducts “cold calling” of all women who self-reported smoking in the last 7 days during their initial antenatal “booking in” appointment (usually around 10 weeks gestation). Using information stored on the DMR, the midwife pre-screens women for eligibility (eg, self-report smoking, 16 years or older) and telephones them to invite them to participate in the study. With their verbal consent, the details of interested women are recorded and forwarded to the research team.

Antenatal staff of the Tasmanian Health Service (including physicians and midwives) provide study information (in the form of a flyer) to eligible participants during antenatal appointments. With their consent, the contact details of interested women are forwarded to the research team. In addition, the study is advertised through flyers placed in general practitioner (GP) clinics, outreach centers and community hubs across Tasmania. Informal advertising via social media (eg, Facebook) and television and radio interview exposure may also be utilized. Consequently, potential participants could also self-refer to the study by contacting the researchers directly.

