### Eligibility Criteria

Women who express interest in participating in the study (either self-refer or consent to a health professional forwarding their contact details to research staff) are contacted by research staff and screened for eligibility using a previously validated protocol [24]. To be eligible for study entry, women must be (1) pregnant (20 weeks gestation or less); (2) at least 16 years of age; (3) self-report as being a current smoker (“even a single puff in the last 7 days”); (4) attending routine antenatal care provided by the Tasmania Health Service or participating GP center (Tasmanian, Australia); and (5) be able to attend a minimum of 3 appointments at 1 of the 3 data collection sites across Tasmania (Launceston General Hospital, Royal Hobart Hospital, or Mersey Community Hospital). Women younger than 18 years (but 16 years or older) require the consent of their parent, guardian, or senior antenatal health provider to participate in the study.

Potential participants are excluded from study entry if they self-report as non-smoking (ie, “have not smoked, even a single puff in last 7 days”) or if they have a cognitive or intellectual impairment that will inhibit fulfillment of participation requirements (eg, completion of surveys and/or attend organized study appointments). Participants who are found to be “gaming” (eg, those who tell researchers they are pregnant and/or smoking untruthfully to enroll in study) are also excluded from further participation and their data discarded. All participants are asked to nominate and are encouraged to bring along to study visits a support person, preferably a person they co-habit with (eg, spouse, father of child, or family member).

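### Hypothesis 4 rests a claim that incentives beat usual care on one non-concurrent 2011-2015 average whose comparability with the trial volunteers is not established; it can serve only as an exploratory benchmark

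*Protocol article*

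**What the plan says.** The third aim (Objectives) and Hypothesis 4 (Planned Analyses) put the question as one of superiority: "providing incentives for pregnant smokers to quit is more effective than" usual antenatal cessation support. The analysis of H4 is one sentence. "The quit rates of participating women will be compared" with a single external figure, the participants' rates being "compared to the average quit rate of a historical control of women receiving antenatal care by the Tasmanian Health Service from 2011 to 2015".

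The trial itself is a "controlled 2-group (control and treatment) trial design". Under Interventions, both groups receive vouchers when the woman verifies as quit; the groups differ only in whether the support person is also rewarded.

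Other sections fix who the trial women are and how their outcome is measured:

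- **Recruitment.** A research midwife "conducts “cold calling” of all women who self-reported smoking in the last 7 days during their initial antenatal" appointment; women may also be referred by staff or refer themselves (Participant Recruitment).
- **Eligibility.** Women must be at 20 weeks or less, aged 16 or older, smoking within the past 7 days at screening, and must "be able to attend a minimum of 3 appointments at 1 of the 3 data collection sites across Tasmania" (Eligibility Criteria).
- **Outcome.** Smoking status is "as determined by self-report 7-day point prevalence, and carbon monoxide (CO) less than 7 particles per million (ppm) at the end-of-pregnancy time point" (Objectives).
- **Loss of contact.** If a participant cannot be reached, "it is presumed they are smoking" (Monthly Telephone Calls and Verification Visits).

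**The concern.** With no untreated or usual-care group in the trial, everything H4 concludes depends on whether the 2011-2015 figure is what these same women would have achieved without incentives. The article gives no ground for that. The trial women are selected in several ways, are followed in a later period, and receive more contact than usual care in addition to the vouchers. Their abstinence is held to a strict definition that may or may not have been used for the historical figure.

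If the plan is followed as written, a difference produced by volunteering, calendar time, monthly contact or outcome definition would be reported as an effect of incentives. Equally, a real effect could be hidden by stricter ascertainment in the trial. Either way the stated conclusion for the third aim would not be earned.

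**Working it through.** H4 states no rate, sample size, alpha, power or test, so there is no figure of the plan's own to reproduce. The check has two parts: setting the two sides of the comparison next to each other, and an illustration of what the differences could do.

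**1. The two sides**

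| Feature | Trial participants | 2011-2015 comparator |
|---|---|---|
| Period | Recruited over 18 months of alternating 3-month blocks | Five-year average, non-concurrent |
| Entry | Volunteers, some self-referred | Women in Tasmanian Health Service antenatal care; no restriction described |
| Smoking at entry | Within 7 days of screening, so women who quit between booking and screening are excluded | Denominator not stated |
| Gestation, age, attendance | 20 weeks or less; 16 or older; at least 3 visits | Not stated |
| Other contact | Resource pack, review of a knowledge quiz, monthly calls | Not stated; the third aim describes usual care as brief advice and referral |
| Outcome | Self-report plus CO below 7 ppm (primary outcome; H4 names no other) | Ascertainment and time point not stated |
| Lost contact | Counted as smoking | Not stated |
| Adverse outcomes | Data withdrawn unless the woman asks to continue (Discussion) | Not stated |

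The directions differ. Volunteering and extra contact would probably raise the trial rate. Exclusion of early quitters would probably lower it. CO verification and counting lost women as smokers would also lower it relative to the comparator if the historical rate is unverified self-report.

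**2. Illustration: bias in favour of H4**

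Inputs:

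- n = 108, the total sample size planned for H1.
- Historical rate p0 = 9%, the usual-care rate at end of pregnancy that the article quotes from the cited incentivised-support trial. It is not the Tasmanian rate and is used only as an example. The range 5% to 15% is also shown.
- Assumed test: exact one-sample binomial against a fixed p0, one-sided 0.025.
- Assumed true effect of incentives: none. Assumed advantage of volunteers: 5 or 10 percentage points.

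Formula: the critical count r is the smallest number with P(X ≥ r | n, p0) ≤ 0.025. The false-positive probability is P(X ≥ r | n, p0 + shift), with X binomial.

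| p0 | r | Exact alpha | Shift +5 points | Shift +10 points |
|---|---|---|---|---|
| 5% | 11 | 0.020 | 0.52 | 0.94 |
| 9% | 17 | 0.016 | 0.34 | 0.84 |
| 15% | 25 | 0.016 | 0.24 | 0.71 |

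**3. Illustration: bias against H4**

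Suppose the historical 9% is unverified self-report and the true trial quit rate is 20%. If a share m is missing and a share f of reported quits fails CO, the recorded rate is 0.20 × (1 − m) × (1 − f). All shares are assumed.

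| m | f | Recorded rate | Probability of at least 17 of 108 |
|---|---|---|---|
| 0 | 0 | 20.0% | 0.89 |
| 10% | 10% | 0.20 × 0.90 × 0.90 = 16.2% | 0.59 |
| 20% | 10% | 0.20 × 0.80 × 0.90 = 14.4% | 0.39 |
| 30% | 25% | 0.20 × 0.70 × 0.75 = 10.5% | 0.06 |

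**4. Both together**

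Take an assumed 30% self-reported quit rate, of which 80-90% pass CO and 85-95% attend. The recorded rate is 0.30 × 0.80 × 0.85 = 20.4% to 0.30 × 0.90 × 0.95 = 25.7%, a penalty of about 4.3 to 9.6 points. Against a volunteer advantage of 5 to 10 points, the net bias runs from 5 − 9.6 = −4.6 to about 10 − 4.3 = +5.7 points. The sign is not determined even within these ranges.

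**The case against.** The strongest defence is that this is a condensed article. The historical figure is cited to a source that is not shown, and matching, trend adjustment and confidence intervals are commonly left to a full protocol or analysis plan. H4 is also the last hypothesis, is openly called a historical control, and carries no weight in the sample size, which is set for H1.

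Much of this stands, and it limits what can be said. A reader might infer three stronger things that the documents do not support:

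- **That the comparator is every woman in antenatal care.** The text does not say so, and a quit rate implies a denominator of smokers.
- **That the outcomes are known to differ.** The only routine smoking measure described is self-report at booking, used to find recruits. It does not show how late-pregnancy smoking was recorded in 2011-2015. The documents support only that alignment is not established.
- **That the comparison is biased in H4's favour.** If the historical rate is self-reported, the CO and missing-data rules make a positive result harder to reach, not easier.

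The defence does not rescue the conclusion. The comparator and the superiority wording are fixed in the article and are not details left for later. Even if the historical rate turned out to be CO-verified and restricted to smokers, volunteer selection, the earlier period and the added contact would remain.

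**Conclusion.** The concern holds in this form: H4 as written cannot support a conclusion that incentives are more effective than usual care. It compares a self-selected, eligibility-restricted cohort that also receives extra contact with one non-concurrent average, with no restriction or adjustment described and no concurrent usual-care group. The sign and size of the bias are unknown. A volunteer advantage of 5 to 10 points alone would give a false-positive probability of 0.34 to 0.84 at a 9% historical rate (0.24 to 0.94 across historical rates of 5% to 15%). Stricter ascertainment alone could cut the power for a true 20% quit rate from 0.89 to between 0.59 and 0.06. These figures rest on assumed rates, on n = 108, and on a test that the article does not specify. They show sensitivity and do not estimate the actual bias.

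A descriptive benchmark remains legitimate. H1, and the other comparisons that do not use the historical figure, are unaffected.

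**What to change.** 1. As far as the source allows, restrict the historical group to women smoking at booking, aged 16 or older and booked by 20 weeks, across the statewide catchment. Do not limit it to the three hospitals: those are data collection sites, while recruitment is statewide and includes participating GP centers.
2. Compare at the same time point with the same outcome definition, for example self-report in both cohorts, and show the CO-verified trial rate alongside. State that trial self-report is linked to a voucher while historical self-report presumably was not, so even this match is imperfect.
3. Give the difference with a 95% confidence interval that includes the comparator's sampling error.
4. Report H4 as an exploratory benchmark, and do not conclude from it that incentives are more effective than usual care.
5. If only an aggregate historical rate can be obtained, make the change of label and wording alone.

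Cost: the wording change costs nothing. An aligned extract needs work on the record system, and possibly further approval, because the access described covers recruitment and checks on participants. Recruitment is closed, but data collection was still under way when the article was written, so this is an analysis-stage change. The downside is a weaker claim for the third aim.
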